**Table 1 Tab1:**
[figure not shown]
SPIRIT participant timeline

*Abbreviations*: *BPSD* Behavioural and psychological symptoms of dementia, *NPI-NH* Neuropsychiatric inventory nursing home version, *ADCS-ADL-sev* Alzheimer’s Disease Cooperative Study Activities of Daily Living scale for Severe impairment, *PCTB* Professional Care Team Burden (PCTB) Scale, *MMSE* Mini-Mental State Examination

**Table 2 Tab2:** Trial Registration Data Set of the MAKS-s study

Data category	Information
Primary registry and trial identification number	ISRCTN15722923
Date of registration in primary registry	07/08/2019
Secondary identifying numbers	GKV-SV339
Source(s) of monetary or material support	German National Association of the Statutory Health Insurance and Long-Term Care Insurance Funds (GKV-Spitzenverband)
Primary sponsor	German National Association of the Statutory Health Insurance and Long-Term Care Insurance Funds (GKV-Spitzenverband)
Secondary sponsor(s)	–
Contact for public queries	[name]. [name] ([contact])
Contact for scientific queries	[name]. [name] ([contact])
Public title	MAKS-s – multimodal psychosocial intervention for people with severe dementia in inpatient care: a cluster-randomized controlled trial
Scientific title	MAKS-s – multimodal psychosocial intervention for people with severe dementia in inpatient care: a cluster-randomized controlled trial assessing the effects on behavioral and psychological symptoms, quality of life, and activities of daily living of people with severe dementia as well as caregiver burden
Countries of recruitment	Germany
Health condition(s) or problem(s) studied	severe dementia, professional care team burden
Intervention(s)	Intervention group: psychosocial group intervention Control group: treatment as usual
1.Key inclusion and exclusion criteria	Ages eligible for study: senior; Sexes eligible for study: all
	Inclusion criteria: 1. Psychometric verification of severe dementia syndrome: Mini Mental State Examination (MMSE) Score between 0 and 9 2. Informed consent for study participation.
	Exclusion criteria: 1. Mild to moderate dementia respectively no cognitive impairment (MMSE > 9) 2. Cognitive decline due to diseases other than dementia (e.g. schizophrenia or Korsakoff) 3. Severe hearing impairment 4. Severe visual impairment 5. Permanently bedridden persons 6. History of severe major depression 7. History of more than one stroke 8. No verbal communication in German possible
Study type	Cluster-randomized controlled multi-center intervention study
Date of first enrollment	01/12/2019
Target sample size	144
Recruitment status	ongoing
Primary outcome(s)	1. Quality of life, measured by QUALIDEM 2. Behavioural and psychological symptoms of dementia, measured by Neuropsychiatric Inventory Nursing Home Version (NPI-NH)
Key secondary outcomes	1. Activities of daily living measured by ADCS-ADL-severe 2. Dementia-related caregiver burden of the nursing and care staff, measured by Professional Care Team Burden Scale (PTCB) 3. Days of incapacity for work of nursing and care staff, measured by documentation of the employer 4. Extent of implementation and voluntary continuation of the intervention in follow-up period, measured by a self-developed questionnaire

### Sample size estimation

#### Primary target group

A power analysis was computed on the basis of the authors’ previous experience with the pilot study MAKS-s ([name]: Modification and implementation of the MAKS-aktiv! therapy with severrly demented people: a pilot experiment, unpublished master´s thesis, Friedrich-Alexander University Erlangen-Nürnberg). For this purpose, the effects of the subscales “mood”, “disturbing behaviour”, and “social behaviour” of the NOSGER (“Nurses’ Observation Scale for Geriatric Patients”) [27] were pooled. The result was an effect size of Cohen’s *d* = 0.52. The beta-error was set to four times the size of the alpha error (α = .05), as proposed by Cohen [28]. This resulted in a power of .80.

Under these conditions, an evaluation sample of 114 individuals (57 per group, 6 per nursing-home) was deemed necessary. On the basis of the previous MAKS study [10], we expect a drop-out rate (mainly caused by death or being bed-ridden) of 20% across 6 months. This means a total of 144 people with severe dementia has to be included in the study. To achieve this goal, only nursing homes with at least 40 residents are being included in the project. This could be deduced from the following considerations:
In nursing homes in Germany, 38.8% of residents suffer from severe dementia [1]. This means 15 out of 40 individuals.In the “MAKS aktiv” study, the rate of bedridden and/or blind/deaf residents was 26% [10]. In the group of severe dementia cases, this rate was 40%. This left 9 of the 15 people with severe dementia suitable for intervention.It can be assumed that at least 70% of the participants will be willing to participate after the legal representatives have been informed [10]. Thus, 6 of the 9 suitable PWSDs can be included in the study.

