### Study design and setting

A two-armed cluster-randomised, controlled, multicentre, prospective longitudinal study with a waitlist control group design will be conducted to test the abovementioned hypotheses.

The nursing homes are located in five areas (German federal state): Bavaria, Baden-Württemberg, Thuringia, Rhineland-Palatinate, and Saarland. All nursing homes (clusters) participating in the study will be randomly assigned to the intervention or control groups at baseline (through random selection) by our cooperation partner “Institut für Medizininformatik, Biometrie und Epidemiologie (IMBE)” at the Friedrich-Alexander University Erlangen-Nürnberg. The clusters will be allocated by applying a tree-step stratification process by using “protective versus non-protective ward”, “area”, and “nursing home size” in decreasing order to balance the structural parameters.

The contact people in each nursing home are trained by the study headquarters with respect to the study protocol, instruments, and screening procedure before randomisation. Informed consent from the legal representatives of the PWSDs and the nursing staff (i.e., trained nurses) and care staff (i.e., staff with no medical training) will also be obtained before randomisation. Nursing homes will be informed about their group assignment in written form by the study headquarters. In addition, the nursing homes in the intervention group will receive further training on the implementation of the MAKS-s intervention. This treatment will be performed through the 6-month intervention phase. The nursing homes in the control group will not carry out any specific treatment but will continue providing “care as usual”.

Because we are investigating a non-pharmacological intervention, not everybody participating in the study can be blinded. Due to the severity of dementia, we can assume that the PWSDs will be blind to the conditions of the study. The therapists performing the MAKS-s intervention cannot be blinded. The raters (nursing staff) will be “semi-blinded”. They will know about the group assignment but will have no knowledge of the intervention. The testers, who are trained students from the study headquarters, who will conduct the tests, will be completely blinded.

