### Strengths and limitations of the study design

The study design offers several strengths. The external validity of the study is high because of the naturalistic setting in nursing homes with nursing staff and the recruitment of nursing homes that are in different federal states of Germany, are in urban and rural regions, and are run by a wide variety of organisations (profit, non-profit, local authorities). Also the duration of the intervention of 6 months, the use of a manualised treatment, and the focus on two target groups (PWSDs and the nursing and care staff) have rarely been applied in international studies [15, 25, 49–51].

Another strength of the current study is the cluster randomisation. We decided to use cluster randomisation rather than randomisation because of the secondary target group. If we were to have a treatment group and a control group in the same nursing home, we could not observe any effect of the intervention on the formal caregivers because the caregivers may be responsible for both the people in the intervention group and the people in the control group. Furthermore, the intervention could not be withheld from any individual working in a nursing home without the possibility of “contaminating” the control group [52]. In order to avoid a systematic difference between the two arms of the study by chance, a three-step stratification process is being conducted to allocate the nursing homes. At the same time, to avoid a recruiting bias, recruitment will be completed before randomisation.

However, a limiting bias can occur. Because we are conducting a non-pharmacological intervention, the nurses who carry out the assessments (raters) are not completely blind to the conditions of the study because they know about the group assignment.

Because the study deals with PWSDs, due to the severe cognitive impairment of the participants, we could only use proxy-based ratings from an observer’s perspective. The perspective of the PWSDs themselves cannot be taken into account.

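### The sample size of 114 makes no allowance for randomising nursing homes, so the stated power of .80 is not supported

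*Protocol article*

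**What the plan says.** Under Study design and setting, the protocol article makes the home the unit of allocation: "All nursing homes (clusters) participating in the study will be randomly assigned to the intervention or control groups at baseline". The Discussion presents this as an advantage: "Another strength of the current study is the cluster randomisation".

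The sample size for residents (Sample size estimation, Primary target group) rests on three inputs:

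- the effect size: "The result was an effect size of Cohen’s *d* = 0.52", pooled from three NOSGER subscales in a pilot study;
- the error rates: "The beta-error was set to four times the size of the alpha error (α = .05"), followed by "This resulted in a power of .80";
- from these, "an evaluation sample of 114 individuals (57 per group, 6 per nursing-home) was deemed necessary".

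A "drop-out rate (mainly caused by death or being bed-ridden) of 20% across 6 months" is then allowed for: "This means a total of 144 people with severe dementia has to be included in the study". Recruitment strategies sets the number of homes at 24 or more, and Eligibility of participants has each home recruit until six residents are consented. The sample size section gives no ICC, no design effect and no sidedness. Homes enter it only through the count of six per home and the feasibility argument for a minimum home size.

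**The concern.** Residents of one home share staff, ward routine and activities. In the intervention arm they also share the group sessions. NPI-NH and QUALIDEM are proxy ratings by care staff of that same home, so a rater's habits are shared as well. Scores within a home will be correlated, and 114 such residents carry less information about the treatment difference than 114 independent ones.

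If the calculation ignores this, the trial has less power for its own target effect than it claims. A non-significant result would then be read as evidence against MAKS-s when the trial had a substantial chance of missing an effect of the planned size. The .80 is also the stated justification for enrolling 144 people with severe dementia through their legal representatives.

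**Working it through.** **Inputs from the protocol article.** d = 0.52; alpha .05; power .80; 57 per group; 20% drop-out; 24 homes; six enrolled per home. Two-sided testing is taken as the base case because sidedness is not stated.

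**Step 1: reproduce the stated figure with independent residents.**

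n per group = 2 × ((1.96 + 0.84)/0.52)² = 58.05, rounded up to 59. The exact t-test needs 60, since 59 gives 0.7998. At 57 per group (112 df) power is 0.786, which is .80 to within rounding. The stated 57 is therefore already slightly below the individually randomised requirement.

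Drop-out: 114/0.8 = 142.5, so 143; the plan's 144 is 24 × 6.

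**Step 2: cluster size at analysis.**

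114/24 = 4.75 evaluable residents per home. Six per home is the enrolment figure (144/24 = 6). Taken literally, 114 at six per home would mean 19 homes, not 24.

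**Step 3: allow for clustering.** The ICC is an assumption, because the article gives none.

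- Design effect DE = 1 + (4.75 − 1) × ICC
- Noncentrality = 0.52 × √(57/(2 × DE))
- Power from the noncentral t with 24 − 2 = 22 df, two-sided .05

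Worked case, ICC 0.05: DE = 1 + 3.75 × 0.05 = 1.1875; noncentrality = 0.52 × √(57/2.375) = 2.547; power 0.683.

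| Assumed ICC | DE | Effective N (114/DE) | Power, 22 df | Power, 112 df | d detectable with 80% power, 22 df |
|---|---|---|---|---|---|
| 0 | 1.00 | 114 | 0.756 | 0.786 | 0.55 |
| 0.02 | 1.08 | 106 | 0.725 | 0.756 | 0.57 |
| 0.05 | 1.19 | 96 | 0.683 | 0.714 | 0.60 |
| 0.10 | 1.38 | 83 | 0.619 | 0.651 | 0.64 |
| 0.20 | 1.75 | 65 | 0.519 | 0.548 | 0.73 |

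Comparing the two power columns separates the causes. About 3 points are lost through having only 24 randomised units; the rest is correlation. Both columns are below .80 throughout.

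**Step 4: what baseline adjustment could return.** With an assumed baseline–follow-up correlation r = 0.5 and the ICC unchanged after adjustment, the effective d is 0.52/√(1 − 0.25) = 0.60. Power on 22 df is then 0.840 (ICC 0.02), 0.803 (ICC 0.05) and 0.743 (ICC 0.10).

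**Step 5: scale of the gap in residents.** By the normal formula with 4.75 per home, 80% power at d = 0.52 needs 138 evaluable residents (138/0.8 = 172.5, so 173 enrolled) at ICC 0.05, and 160 evaluable (200 enrolled) at ICC 0.10.

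**The case against.** The strongest reply is that the absence of a design effect is inferred. Sidedness is not stated and the hypotheses are directional. A one-sided test needs 2 × ((1.645 + 0.84)/0.52)² = 45.7 per group; multiplied by 1 + 5 × 0.05 = 1.25 (six per home, ICC 0.05) this gives 57.2, which matches 57 as well as the two-sided reading does. That is numerically true, so the match to 57 is not by itself proof. But this reading needs two inputs the article nowhere states, a one-sided test and an ICC of 0.05. The article presents 114 as following from d, alpha and power alone.

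Second, the size of the loss depends on an unknown ICC. This stands: at 0.01 to 0.02, correlation alone costs only about 1.5 to 3 points, and about 3 further points in the 22 df figures are due to degrees of freedom.

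Third, the planned multiple regression may adjust for baseline and recover the loss. It may: with r = 0.7 assumed, power is 0.89 at ICC 0.10 and 0.80 at ICC 0.20. But the sample size section claims no such credit, so it cannot support the .80 as written.

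Fourth, the NOSGER origin of d is disclosed, and six per home may be only loose wording. Both are fair. They are secondary, and the main point does not depend on them.

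**Conclusion.** The point holds. On the stated inputs, 57 per group delivers 0.786 only if residents are independent and the test is two-sided, and the design randomises homes. Any positive ICC lowers power from there. On 22 df and without baseline adjustment, it is 0.73 to 0.52 over an assumed ICC range of 0.02 to 0.20, and the effect detectable with 80% power rises from 0.55 at ICC 0 to 0.60 at ICC 0.05 and 0.73 at ICC 0.20.

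The direction is firm for a two-sided test without covariate credit; the size rests on the assumed ICC. Baseline adjustment or a one-sided test could bring power back near .80 at a modest ICC, but neither is claimed in the calculation. The effect size itself also rests on carrying a NOSGER result over to NPI-NH and QUALIDEM.

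**What to change.** Keep 24 homes and 144 residents, and rewrite the power paragraph in the protocol and analysis plan:

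- Withdraw the unconditional .80. Report the design effect 1 + (4.75 − 1) × ICC, the power and the detectable effect for ICC 0.02 to 0.20 on 22 df, and give the source of whichever ICC is taken as most plausible.
- State whether the test is one- or two-sided.
- Give 4.75 evaluable residents per home beside the 114, and keep six for enrolment.
- State that d = 0.52 was obtained on NOSGER and is assumed to apply to NPI-NH and QUALIDEM.
- If baseline adjustment is to be credited, name the assumed correlation and show power with and without it.

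The analysis behind these figures must itself account for homes. A regression that ignored clustering would inflate the type I error and would not restore the power.

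The cost is one paragraph and a less favourable power figure. No extra homes or residents are needed.

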### Recruitment strategies

Nursing homes from the postulated size in the recruitment areas are identified by means of their websites. Information material is sent to these nursing homes by post. Two weeks later, all the facilities that have been contacted are called by telephone and asked whether they are willing to participate. Cooperation contracts are signed with the nursing homes that are interested in participating in the study. After at least 24 nursing homes have signed a cooperation contract, recruitment will be completed.

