### Eligibility of participants

All residents of the participating units in the 24 nursing homes will be included in the screening process. Additionally, in every nursing home, the members of the nursing and care staff who are involved most in the care of the participants of the study will be selected. The screening process will be conducted by trained nursing staff working in the participating nursing homes.

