#### Primary target group

All residents will undergo a three-step standardised screening process to determine their suitability for the project. In the first step of the screening process, all residents fulfilling at least one of the following criteria are excluded: bedridden, blind, deaf, no sufficient knowledge of German, more than one stroke, severe depression, schizophrenia, an addictive disorder, concrete plan to leave the facility. In the second step, cognitive performance is assessed. Individuals who definitely have a MMSE (Mini-Mental State Examination) figure of over 9 points (estimated by the nursing staff) are excluded. Every other person is tested with the MMSE. Individuals who attain more than 9 points are excluded. All individuals who are potentially eligible to participate in the study are put on a list and randomised by a randomising list from our cooperation partner IMBE. After the randomisation, the nursing home staff apprise the legal representatives of the eligible individuals in the order of the randomisation list. After the legal representative provides written informed consent, the PWSD is included in the study. This process is performed until six people per nursing home give their consent.

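### The 40-resident minimum per home does not assure six participants per home, or 144 in total, under the protocol's own screening rules

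*Protocol article*

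**What the plan says.** All places are in the protocol article.

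- **Sample size estimation, Primary target group.** An evaluation sample of 114 is required. With 20% loss over 6 months, 144 must be included. The entry rule for homes follows: "To achieve this goal, only nursing homes with at least 40 residents are being included in the project". Its derivation has three steps: "In nursing homes in Germany, 38.8% of residents suffer from severe dementia [1]. This means 15 out of 40 individuals"; then, counting only bedridden, blind or deaf residents as unsuitable, "In the group of severe dementia cases, this rate was 40%. This left 9 of the 15 people with severe dementia suitable for intervention"; then "It can be assumed that at least 70% of the participants will be willing to participate after the legal representatives have been informed", which gives 6 of the 9.
- **Eligibility of participants.** The screening frame is narrower than the home: "All residents of the participating units in the 24 nursing homes will be included in the screening process".
- **Eligibility of participants, Primary target group.** The first screening step removes anyone who is or has: "bedridden, blind, deaf, no sufficient knowledge of German, more than one stroke, severe depression, schizophrenia, an addictive disorder, concrete plan to leave the facility". Legal representatives are then approached in a random order of residents until six per home have consented.
- **Recruitment strategies.** "After at least 24 nursing homes have signed a cooperation contract, recruitment will be completed".
- **Study design and setting; Strengths and limitations.** Consent is obtained, and recruitment completed, before the homes are randomised.

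**The concern.** The entry rule exists to secure six participants per home, but its derivation does not match the procedures that will produce those participants.

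1. **Exclusions.** Insufficient German, more than one stroke, severe depression, schizophrenia, an addictive disorder and a planned departure are all screened out. None is deducted in the derivation.
2. **Base.** The derivation starts from all residents of the home, whereas screening covers only its participating units.
3. **An average used as a floor.** Six is roughly what a 40-resident home yields on average. Some such homes will yield fewer. Because inclusion stops at six, a home with surplus candidates cannot make up for one that falls short, and 24 × 6 = 144 leaves no reserve if recruitment ends at 24 homes.

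At stake are the 144 to be included and the 114 to be evaluated. If homes are closed on the number of contracts, a shortfall becomes visible only once screening and consent are under way in a set of homes that is no longer growing.

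**Working it through.** **Inputs from the protocol:** 40 residents; 38.8% severe dementia; 40% of these unsuitable; 70% consent; at most 6 per home; 24 homes; 20% loss; 114 evaluable; d = 0.52; α = .05.

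**1. The protocol's own figure reproduces.**
- With its rounding: 15 × 0.60 = 9; 9 × 0.70 = 6.3, taken as 6; 24 × 6 = 144.
- Unrounded: 40 × 0.388 × 0.60 × 0.70 = 6.52.
- 114 / 0.80 = 142.5, and 144 is the next number that fills whole homes of six.

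**2. Margin at the 40-resident floor.**
- The largest further exclusion that keeps the expected yield at six is 1 − 6/6.3 = 4.8% (rounded chain) or 1 − 6/6.52 = 8.0% (unrounded).
- The smallest share of a 40-resident home that the participating units may cover, at equal prevalence of severe dementia, is 6/6.52 = 92%.

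The protocol gives neither quantity. Assumed further exclusions of 10%, 20% and 30% give expected yields of 5.87, 5.21 and 4.56. Assumed unit coverage of 90%, 75% and 50% gives 5.87, 4.89 and 3.26.

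**3. Effect of the cap, with no further exclusions and the whole home screened.** Let the yield of a home with n residents be X ~ Binomial(n, 0.388 × 0.60 × 0.70 = 0.163), and let the number included be min(X, 6). Then total included = 24 × E[min(X, 6)], and evaluable = 0.80 × that total.

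| Residents in each of 24 homes | P(home reaches six) | Mean included per home | Included | Evaluable |
|---|---|---|---|---|
| 40 | 0.65 | 5.33 | 128 | 102 |
| 50 | 0.85 | 5.74 | 138 | 110 |
| 60 | 0.94 | 5.91 | 142 | 113 |
| 70 | 0.98 | 5.97 | 143 | 115 |

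This step needs no assumed exclusion rate. It uses the protocol's rates and adds only binomial variation between homes. In a milder version, every home has exactly 9 suitable residents and only consent varies. Then P(six) = 0.73, the total is about 134 and about 108 are evaluable.

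**4. Both effects together (assumed 20% further exclusions).** Homes of 40 give 113 included and 90 evaluable; homes of 50 give 127 and 102; homes of 70 give 140 and 112.

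**5. Effect on power.** For a two-sided t-test with d = 0.52, ignoring clustering, power is 0.79 at 114 evaluable (57 per arm) and 0.74 at 102.

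**The case against.** The strongest reply is that 40 residents, 24 homes and 70% consent are all stated as minima. The allocation is stratified by nursing home size, so sizes are expected to vary, and the figure of 128 needs all 24 homes to sit exactly at the floor. At 60 to 70 residents the capped total is already 142 to 143. An entry rule based on an expected yield is an ordinary feasibility device and was not offered as a guarantee.

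The net effect of the omitted exclusions is also unknown. Table 2 treats schizophrenia as a non-dementia cause of cognitive decline, so such residents may already lie outside the 38.8%. Others may overlap with the 40% who are bedridden, blind or deaf. Participating units may be protective wards with more severe dementia than average: in units covering 75% of a 40-resident home, a prevalence of 47.6% would restore an expected six. The eligibility section also speaks of all residents being screened, which leaves the frame itself unclear.

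All of this stands, and it limits what can be said about size. A reader might infer that six per home and 144 in total will not be reached. The documents do not support that, because they give no rate of further exclusion, no unit sizes, no prevalence within units and no mix of home sizes. For the same reason they do not support any particular higher threshold.

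The reply does not reconcile the derivation with the screening rules. It also does not remove the cap: homes larger than 40 bring the total closer to 144, but with 24 homes never above it.

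**Conclusion.** The point holds in a limited form. The 40-resident rule does not assure six participants per home or 144 overall, because it omits exclusions that screening applies, uses the home where screening uses participating units, and treats an expected 6.3 to 6.5 as if every home reached six. With a cap of six and permission to stop at 24 homes, 144 is a ceiling.

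At the protocol's own rates the cap costs about 16 inclusions (144 − 128) if all homes are at the floor, about 6 at 50 residents and about 1 at 70. These figures assume independent residents, equal home sizes, exactly 24 homes and exactly 70% consent. More homes or better consent would reduce the loss; further exclusions or partial unit coverage would increase it. At the floor, further exclusions above about 5–8%, or unit coverage below about 92% at equal prevalence, are enough to take even the expected yield below six.

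This is a recruitment risk with a modest cost in power. It does not bear on the validity of the analysis. It is worth correcting because the repair is simple.

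**What to change.** 1. **Sample size estimation, Primary target group.** Redo the chain with every exclusion of the first screening step, and with residents of the participating units as the base. State the assumed rate for the added exclusions. Then restate either the minimum size, expressed for the participating units, or the expected number included. The new minimum should follow from the trial's own rates; this review does not propose one.
2. **Recruitment strategies.** Replace closure on the number of signed contracts by closure once 144 residents have written consent, with at least 24 homes, before the homes are randomised. Consent already precedes allocation of the homes in this design, so the rule introduces no knowledge of allocation into recruitment.
3. **Eligibility of participants.** Say whether all residents of a home or only those of participating units are screened.

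The cost is a wording amendment and possibly a few more homes to contact and contract before allocation. If home recruitment has already closed, the remaining step is to restate the expected included and evaluable numbers.
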